### Withdrawal criteria

2.8

#### Investigator-initiated withdrawal

2.8.1

Investigator-initiated withdrawal refers to the removal of a randomized participant from the trial by the investigator due to circumstances that make it inappropriate for the participant to continue. Such participants will be withdrawn and provided with alternative treatments. Reasons include, but are not limited to: (1) Clinical changes: Development of severe comorbidities, complications, or specific physiological changes during the trial that, in the investigator’s judgment, render the participant unfit for continued participation. (2) Safety concerns: Occurrence of a serious adverse event (SAE) or other safety issues that necessitate the cessation of the trial intervention according to the investigator’s assessment. (3) Blinding violations: Cases involving premature unblinding or emergency unblinding must be withdrawn from the study.

#### Participant-initiated withdrawal

2.8.2

Participants have the right to withdraw from the trial at any time. This includes: (1) Withdrawal of consent: The participant explicitly requests to terminate their participation in the trial. (2) Loss to follow-up: The participant does not explicitly withdraw but stops receiving the study medication or attending scheduled assessments and is subsequently lost to follow-up. All participants who discontinue the study early, except in cases of loss to follow-up, should complete subsequent visits according to the study schedule until the study endpoint.

### Trial discontinuation and termination

2.9

Trial discontinuation, including temporary suspension or permanent termination, refers to the cessation of the entire clinical trial before its scheduled completion as per the protocol. The primary objectives of discontinuation are to protect the rights and welfare of participants, ensure the quality of the trial, and avoid unnecessary financial losses.

The clinical trial should be discontinued if any of the following situations occur: (1) Safety Issues: The occurrence of serious safety concerns where the investigator deems that the rights and well-being of the participants may be compromised. (2) Protocol or Implementation Deviations: The identification of major flaws in the clinical trial protocol or significant deviations during implementation that render the evaluation of the drug’s efficacy and/or safety unfeasible. (3) Sponsor Decisions: Request for discontinuation by the sponsor due to reasons such as funding constraints or administrative adjustments. (4) Regulatory Actions: Revocation of trial approval or orders to cease by pharmaceutical regulatory authorities.

### Statistical analysis

2.10

Statistical analyses will be performed using SAS version 9.4 or a higher version.

The analysis populations are defined as follows: the Full Analysis Set (FAS) includes all randomized subjects who receive at least one administration of the investigational drug; the Per Protocol Set (PPS) includes all subjects in the FAS who comply with the study protocol, demonstrate good compliance, have complete primary efficacy endpoint data, do not use concomitant medications affecting efficacy evaluation, and have no major protocol deviations; the Safety Set (SS) includes all subjects who receive at least one administration of the study drug after randomization and have safety assessment data, and will be used as the safety analysis population.

Primary efficacy endpoint analysis: the primary endpoint is the cough relief rate on Day 14, defined as the proportion of subjects with a CSS total score ≤2 at the Day 14 visit and maintained for 48 h ± 2 h. Regardless of whether subjects experience transient relief during the treatment period, the final determination will be based on the CSS status at the Day 14 visit. This endpoint is a binary outcome and will be analyzed using the Cochran–Mantel–Haenszel (CMH) χ^2^ test stratified by center as the primary analysis model, separately in the FAS and PPS populations. Differences in relief rates between groups will be estimated using risk difference (RD), with point estimates, corresponding two-sided 95% confidence intervals, and *p* values reported. In addition, supplementary Logistic regression analyses will be performed with treatment group, center, and baseline CSS score as covariates to assess the robustness of the primary conclusions after covariate adjustment. For missing data of the primary endpoint, the Last Observation Carried Forward (LOCF) method will be used as the primary handling approach. To evaluate the robustness of the primary conclusions under assumptions regarding missing data, multiple imputation (MI) sensitivity analyses will be conducted under the Missing At Random (MAR) assumption, using baseline CSS score, treatment group, center, and all available post-baseline observations as imputation variables to impute missing values. The results obtained from both methods will be reported and compared simultaneously.

Secondary efficacy endpoint analysis: for quantitative variables, descriptive statistics will include number of cases (*n*), mean, standard deviation (SD), minimum, maximum, median, lower quartile (Q1), upper quartile (Q3), and 95% confidence interval (95%CI). Prior to analysis, normality tests will be performed for variable distributions: if the data conform to a normal distribution, inter-group comparisons will be conducted using the independent-samples *t* test, and within-group pre- and post-treatment comparisons will be conducted using the paired *t* test; if the data do not conform to a normal distribution, inter-group comparisons will be conducted using the Wilcoxon rank-sum test, and within-group pre- and post-treatment comparisons will be conducted using the Wilcoxon signed-rank test. For categorical variables, results will be described using frequencies and percentages. When considering the impact of center effects, binary and ordinal variables will be analyzed using the CMH χ^2^ test, and 95% confidence intervals for between-group risk differences will be provided for binary variables; when adjustment for baseline imbalance or other covariates is required, Logistic regression analysis will be used. For time-to-event variables, median time, lower and upper quartiles, and 95% confidence intervals will be described, Kaplan–Meier survival curves will be plotted, and inter-group comparisons will be performed using the log-rank test.

All statistical tests will be two-sided, and *p* < 0.05 will be considered statistically significant.

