#### Inclusion criteria

2.3.1

Participants who meet all of the following criteria will be eligible for enrollment:

(1) Age: Aged 18–65 years (inclusive) at the time of informed consent.(2) Western Medicine Diagnosis: Meeting the diagnostic criteria for PIC.(3) TCM pattern identification: Wind invasion-Dampness obstruction syndrome.(4) Symptom Severity: CSS of ≥ 3.(5) Informed consent: Written informed consent was obtained.

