#### Primary outcome

2.6.1

The primary outcome measure is the cough relief rate after 14 days of treatment. Cough relief is defined as a total CSS (daytime + nighttime) ≤ 2, sustained for at least 48 h ± 2 h. Cough cure is defined as a total CSS (daytime + nighttime) ≤ 1, sustained for at least 48 h ± 2 h. The CSS will be recorded at baseline and daily throughout the study. The inter-group difference in the 14-day cough relief rate will be evaluated according to these diagnostic criteria.

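### The primary risk difference is valid but gives up precision: baseline CSS adjusts the treatment effect only in a supplementary logistic model, which usually reports on a different scale

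*Protocol article*

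**What the plan says.** In section 2.10 (Statistical analysis) of the protocol article, the primary endpoint "will be analyzed using the Cochran–Mantel–Haenszel (CMH) χ^2^ test stratified by center as the primary analysis model", in the FAS and the PPS. The effect measure is the risk difference with a two-sided 95% confidence interval, and no covariate other than centre is named for it.

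Baseline CSS appears in two other places in the same section:

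- In the robustness analysis: "supplementary Logistic regression analyses will be performed with treatment group, center, and baseline CSS score as covariates".
- In the multiple-imputation sensitivity analysis: "using baseline CSS score, treatment group, center, and all available post-baseline observations as imputation variables to impute missing values". That use fills in missing outcomes. It does not adjust the treatment effect, and it plays no part in the LOCF-based primary analysis.

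The endpoint and the entry rule use the same instrument. Section 2.3.1 (Inclusion criteria) requires "Symptom Severity: CSS of ≥ 3". Section 2.6.1 (Primary outcome) states: "Cough relief is defined as a total CSS (daytime + nighttime) ≤ 2". Section 2.10 repeats that threshold for the Day 14 visit. Table 3 scores daytime and nighttime cough 0-3 each, so the total runs from 0 to 6.

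**The concern.** A participant's distance from the success threshold is fixed at entry, and it differs fourfold across the eligible range. A covariate of that kind would normally be expected to predict the outcome. The plan itself treats it as relevant, since it appears in both the supplementary model and the imputation model. Leaving it out of the primary estimate gives up precision that data already collected could supply, in a trial with only 40 participants on placebo.

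The second issue is scale. The supplementary model is meant to show whether the primary conclusion survives covariate adjustment. A logistic model ordinarily reports a conditional odds ratio. That figure can move away from the crude odds ratio even when the arms are perfectly balanced and the risk difference is unchanged, so it is a poor check on a risk difference.

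**Working it through.** **1. Inputs from the article.** Relief rates 88% and 48%, 2:1 allocation, two-sided alpha 0.05, power 0.90, margin 10 points, 71 + 36 evaluable, 80 + 40 enrolled (section 2.7). Six centres (section 2.1). CSS 0-6, entry at 3 or more, relief at 2 or less.

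**2. The plan's own figure.** Unpooled variance with the margin: n(control) = (0.48×0.52 + 0.88×0.12/2) × (1.960 + 1.282)² / (0.40 − 0.10)² = 0.3024 × 10.51 / 0.09 = 35.3, so 36. Treatment: 2 × 35.3 = 70.6, so 71. Dropout: 107/0.9 = 118.9, so 119 against 120 planned. The sample size reproduces and does not depend on this point.

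**3. Required fall.** Baseline minus 2: 1, 2, 3 or 4 points from a baseline of 3, 4, 5 or 6.

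**4. Assumptions, because the article gives no figures.** Baseline mix 35/35/20/10% at CSS 3/4/5/6. The log-odds of relief fall by b per baseline point in both arms, with intercepts set so that the arm averages stay at 88% and 48%.

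**5. Variance that baseline CSS can remove.** Unadjusted variance of the risk difference: 0.88×0.12/80 + 0.48×0.52/40 = 0.00132 + 0.00624 = 0.00756 (SE 0.087). The part due to chance differences in baseline mix is Var[h(x)] × (1/80 + 1/40). Here h(x) = pT(x)/3 + 2pC(x)/3, where pT(x) and pC(x) are the relief rates at baseline x, and 1/80 + 1/40 = 0.0375.

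| b | pT at CSS 3/4/5/6 | pC at CSS 3/4/5/6 | Var[h] | × 0.0375 | share of 0.00756 |
|---|---|---|---|---|---|
| 0 | 0.88 throughout | 0.48 throughout | 0 | 0 | 0% |
| 0.5 | 0.931/0.892/0.833/0.752 | 0.607/0.484/0.362/0.256 | 0.0091 | 0.00034 | about 5% |
| 1.0 | 0.968/0.917/0.802/0.599 | 0.715/0.480/0.253/0.111 | 0.0299 | 0.00112 | about 15% |
| 1.5 | 0.987/0.944/0.791/0.458 | 0.798/0.468/0.164/0.042 | 0.0518 | 0.00194 | about 26% |

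**6. Simulation at 80 versus 40, comparing the risk difference without and with baseline CSS.**

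- Same mix, 3,000 trials per setting, adjustment for baseline CSS. The SD goes from 0.0848 to 0.0834, 0.0868 to 0.0801 and 0.0857 to 0.0745 at b = 0.5, 1.0 and 1.5. Variance falls by 3%, 15% and 24%.
- Mix 35/40/17/8%, 1,500 trials per setting, compared with a centre-stratified Mantel-Haenszel difference. Variance falls by about 0%, 7%, 15% and 23% at b = 0, 0.5, 1.0 and 1.5.
- Six unequal centres with small ones pooled, and centre in the model. Variance falls by about 0%, 5%, 14% and 26%, and the model converged in about 99% of trials.

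The mean risk difference was about 0.40 with and without adjustment, so there was no bias.

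**7. What that buys.** At b = 1.0 the 95% CI half-width goes from 1.96 × 0.0868 = 17.0 points to 1.96 × 0.0801 = 15.7 points. At the planned effect, power against zero exceeds 99% either way. Power against the 10-point margin at b = 1.0, using the SEs 0.0854 and 0.0788 from the second simulation, goes from Φ(0.30/0.0854 − 1.96) = 94% to Φ(0.30/0.0788 − 1.96) = 97%. If the truth were 70% versus 48%, power against zero would be 63/64/65% for CMH and 67/73/79% for the adjusted logistic test at b = 0.5/1.0/1.5. At b = 0 it would be 62% and 64%.

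**8. The scale mismatch.** The marginal odds ratio is (0.88/0.12)/(0.48/0.52) = 7.9. With the same 0.40 risk difference and perfect balance, the conditional odds ratio is about 8.8, 12.0 or 19.3 at b = 0.5, 1.0 or 1.5.

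**The case against.** The strongest reply is that nothing here is wrong. The plan names one primary method, one effect measure and a pre-specified adjusted analysis. A simple primary analysis with an adjusted supportive one is ordinary practice. That stands: randomisation makes the centre-stratified risk difference valid, and simulated type I error was about 4-5%.

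A reader might infer that chance imbalance in severity biases the primary estimate. It does not. If 35% enter at CSS 3, the between-arm difference in that share has an SD of √(0.35×0.65×0.0375) = 9 points, but this is ordinary sampling error that the planned confidence interval already covers. The 9 points also refer to the baseline mix, not to the risk difference.

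Three other stronger readings go beyond the text.

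- Baseline CSS is not otherwise ignored, because it is an imputation variable.
- The article never says that the supplementary model reports an odds ratio. That is inferred from the method, and an SAP could specify standardisation.
- Section 2.2 mentions no stratification of the randomisation, but silence in a condensed article does not prove there is none. The 10-point margin appears only in section 2.7, and section 2.10 sets no test against it, so the margin is no argument for changing covariates.

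A further objection is that the adjusted model may be fragile, with about 80×0.12 + 40×0.52 = 30 expected non-relief outcomes. With six unequal, unpooled centres the logistic model failed or separated in about 30% of simulated trials, and a Firth-standardised risk difference averaged 0.381-0.390 against a true 0.40. This stands as a warning about how to fit the model. It is not a case against adjustment, because with small centres pooled and ordinary logistic regression the problem largely disappeared.

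**Conclusion.** The point holds as one of efficiency and interpretability, not of validity. The planned primary analysis is sound, but it leaves the most obvious prognostic variable out of the estimate, and the planned robustness check probably reports on another scale.

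Under the assumed baseline mix, the loss ranges from nothing, if baseline CSS is unrelated to relief, to about a quarter of the variance at a slope of 1.5. A slope of 1.0 gives about 15%, roughly the precision of 120/0.85 = 141 participants. Both the mix and the slope are assumptions. In the power figures for 70% versus 48%, the adjusted model omitted centre and no centre effect was simulated, so a small part of the difference (0-4% of the variance) can come from centre stratification alone.

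At the planned 40-point effect the decision is unlikely to change. The gain would matter mainly if the true effect were nearer 20 points. The change is worth making because it is cheap, but the trial does not fail without it.

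**What to change.** Before unblinding, pre-specify a marginal risk difference adjusted for baseline CSS. Standardise it from the logistic model already planned: treatment, baseline CSS as a linear term, and centre, with small centres pooled by a rule fixed in advance. Give a robust or bootstrap 95% CI. Preferably make this the primary estimate. At the least, make it the reported output of the supplementary model, so that the robustness check is on the primary scale.

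Keep the centre-stratified CMH analysis as the supportive analysis and as the stated fallback if the model does not converge. Do not use a Firth penalty with unpooled centres, because it can shrink the risk difference.

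The cost is a change of wording and a short program. Table 1 already schedules a pre-treatment CSS, so no data, visits or participants are added. The downsides are slightly more complex reporting and, if a delta-method interval is used, one that can be slightly narrow at this sample size (coverage about 92-95% in simulation).

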### Study design

2.1

A randomized, double-blind, placebo-controlled, parallel-group, superiority clinical trial design will be employed. The study will be conducted across six hospitals in three regions of China: China-Japan Friendship Hospital (Beijing), the Third Affiliated Hospital of Beijing University of Chinese Medicine (Beijing), Wangjing Hospital of the China Academy of Chinese Medical Sciences (Beijing), Huairou Hospital of Beijing Traditional Chinese Medicine Hospital (Beijing), Wuqing District People’s Hospital (Tianjin), and the Affiliated Traditional Chinese Medicine Hospital of Southwest Medical University (Sichuan). Trial monitoring will be conducted on-site, with each study center receiving an initiation visit, a close-out visit, and two routine monitoring visits.

The overall study period spans from November 2024 to November 2027. The initial phase (November 2024 to October 2025) was devoted to protocol development and trial preparation, with no participant enrollment or screening conducted prior to the receipt of ethical approval and trial registration. Participant recruitment and intervention are scheduled between November 4, 2025, and November 30, 2027. The detailed study flow is illustrated in Figure 1. This protocol adheres to the SPIRIT 2025 guidelines and is conducted in accordance with the ethical principles outlined in the Declaration of Helsinki.

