### Randomization and blinding

2.2

A block randomization method will be employed, with the randomization sequence generated by a statistician independent of the study conduct. Using an appropriate block length and a predefined random seed, a randomization sequence for 120 subjects will be generated via SAS 9.4 statistical software. Participants will be assigned to either the SHFS or placebo group at a 2:1 ratio. A randomization table will be generated, listing the drug kit numbers for assignment. Investigators will allocate these numbers to participants in the order they enroll, starting from the lowest number. A competitive enrollment mechanism will be implemented across all participating centers. This study is a double-blind trial; therefore, both investigators and outcome assessors will be blinded to the treatment allocation sequence. The investigational drug and the corresponding placebo will be identical in appearance and packaging. The blinding codes will be prepared in triplicate, sealed, and securely stored by the lead clinical research institution, the statistical unit, and the sponsor, respectively. Unauthorized access to blinding or emergency envelopes is strictly prohibited. Any premature unblinding of the codes will result in the disqualification of the clinical trial. Unblinding will be performed once, at the end of the trial or when necessary for safety reasons.

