### Sample size calculation

2.7

The sample size was estimated based on efficacy data from previous clinical trials. The cough relief rate for Suhuang Zhike Capsule was reported to be 87.75–93.33% (8, 14); thus, the expected relief rate for the Shufeng Huashi formula (π_T_) was estimated at 88%. The relief rate for the placebo, based on previous studies, ranged from 47.76–58.51% (15, 16); therefore, the expected relief rate for the placebo group (π_C_) was set at 48%. A 2:1 superiority design was employed, with a two-sided significance level of *α* = 0.05 and a power of 0.9 (1 − *β* = 0.9). A clinical superiority margin of 10% was considered. Using PASS 21 software for sample size estimation, the calculated requirement was 71 participants for the treatment group and 36 for the control group. Accounting for a 10% dropout rate and potential unforeseen data loss during trial execution, a total of 120 participants will be enrolled, with 80 in the treatment group and 40 in the control group. Participants will be recruited through outpatient clinics and advertisements.

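### At the planned rates the supplementary logistic model has about four non-relieved participants per term; if fitted by ordinary maximum likelihood, its odds ratio would run about 17–25% high, which Firth's method would largely remove

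*Protocol article*

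**What the plan says.** Section 2.10 makes the CMH test stratified by centre the primary analysis, with the risk difference as the effect measure. As a robustness check after covariate adjustment it adds: "supplementary Logistic regression analyses will be performed with treatment group, center, and baseline CSS score as covariates". SAS 9.4 or later is the software. The section does not say how the logistic model is to be estimated, how centre is coded, or what happens with very small centres.

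Three other places determine how much information that model has:

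- Section 2.1 (Study design): "The study will be conducted across six hospitals in three regions of China".
- Section 2.2 (Randomization and blinding): "A competitive enrollment mechanism will be implemented across all participating centers". No minimum per centre is given.
- Section 2.7 (Sample size calculation): 120 participants, "with 80 in the treatment group and 40 in the control group". The relief rate for SFHS "was estimated at 88"%, and that for placebo was taken as 48%.

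**The concern.** The precision of a logistic model depends on the smaller of the two outcome groups, here the participants without relief. When there are few of them per fitted term, ordinary maximum likelihood pushes a real log odds ratio away from zero. The covariate list is fixed in the article and can be set against the article's own expected rates, and the resulting count is low.

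At stake is the size of a supplementary odds ratio. An adjusted value that is inflated by the method could be read as an effect that grows stronger after adjustment. A second, smaller matter is that competitive enrolment may leave some centres with a handful of participants. A centre in which everyone is relieved has no finite maximum-likelihood coefficient.

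**Working it through.** **Step 1. Reproduce the plan's sample size, to confirm the inputs.** Section 2.7 gives 88% and 48%, 2:1 allocation, "with a two-sided significance level of" 0.05, power 0.9, and a margin: "A clinical superiority margin of 10% was considered". With unpooled variance:

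n_C = [0.48×0.52 + (0.88×0.12)/2] × (1.960 + 1.282)² / (0.40 − 0.10)² = 35.30

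This gives 36 control and 2 × 35.30 = 70.6, so 71 treatment, as stated. Dividing by 0.9 for dropout gives 40 and 79; 80 + 40 keeps the ratio. The planning rates are therefore used as the article uses them.

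**Step 2. Count terms and outcomes.**

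- Terms: treatment 1 + centre 5 (six hospitals, fixed categories) + baseline CSS 1 (linear) = 7.
- Non-relieved at 120: 80×0.12 + 40×0.52 = 9.6 + 20.8 = 30.4, and 30.4/7 = 4.3 per term.
- Non-relieved at 107: 71×0.12 + 36×0.52 = 27.2, and 27.2/7 = 3.9 per term.

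**Step 3. True odds ratio at the planned rates.** (0.88/0.12)/(0.48/0.52) = 7.94, log 2.072. Where CSS or centre affects outcome, the true conditional odds ratio is larger. Each comparison below is against that conditional value, so the ordinary gap between marginal and conditional odds ratios is not counted as bias.

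**Step 4. Simulate the model at the planned rates.** There were 4,000 trials per scenario. The following are assumptions, since the article gives no figures: baseline CSS 3/4/5/6 in proportions 35/35/20/10%, CSS log-odds slope 0 to 0.8, between-centre SD 0 to 0.5 on the logit scale, and the expected centre sizes shown. For maximum likelihood (ML), centres with a single outcome were dropped when estimating treatment, because they carry no information on it.

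| Scenario | True OR | ML, median OR / true | Firth, exp(mean bias) | Trials with a non-finite coefficient |
|---|---|---|---|---|
| Equal centres, no CSS or centre effect | 7.94 | 1.19 | 1.002 | 3% |
| Equal, slope 0.4 | 8.47 | 1.19 | 1.004 | 3% |
| Equal, slope 0.4, SD 0.5 | 9.31 | 1.23 | 1.009 | 9% |
| 40/25/20/15/12/8, slope 0.4, SD 0.5 | 9.30 | 1.22 | 1.010 | 26% |
| 60/25/15/10/6/4, slope 0.4, SD 0.5 | 9.30 | 1.20 | 1.003 | 61% |
| 60/25/15/10/6/4, no effects | 7.94 | 1.18 | 1.004 | 56% |
| Equal, slope 0.8, SD 0.5 | 11.19 | 1.27 | 1.005 | 6% |
| N = 107, equal, slope 0.4 | 8.47 | 1.23 | 1.009 | 5% |

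A further set of runs at 88%/48% gave 17–22% for maximum likelihood by median. Firth was within 3% by median, with lower root-mean-square error on the log scale (0.50–0.51 against 0.60–0.63). Most scenarios lie between 17% and 25%; the strongest CSS slope reaches 27%.

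**Step 5. Is this only a small trial, or the model?** The unadjusted 2×2 table has mean log odds ratio 2.124, and exp(2.124 − 2.072) = 1.05. On the same mean scale, the adjusted model in the first row has 2.280, and exp(2.280 − 2.072) = 1.23. Most of the excess comes from the added terms.

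**Step 6. Vary the effect** (48% on placebo, 80/40).

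| SFHS relief | Non-relieved | Per term | ML odds ratio too high by |
|---|---|---|---|
| 78% | 17.6 + 20.8 = 38.4 | 5.5 | about 11% |
| 70% | 24 + 20.8 = 44.8 | 6.4 | about 7% |
| 48% (no effect) | 41.6 + 20.8 = 62.4 | 8.9 | none (ratio 0.99–1.00) |

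**Step 7. Tests and intervals.** With no true effect the Wald test rejected in 4.6–5.2% of trials in one set of runs and 4.6–6.4% in another. The likelihood-ratio test rejected in 5.4–5.7% and CMH in 4.4–4.8%. Wald 95% interval coverage was 93–96%. At the planned rates all three tests reject in more than 99% of trials.

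**Step 8. Small centres.** Overall relief is (2/3)×0.88 + (1/3)×0.48 = 0.747. The chance that a centre of size n has nobody unrelieved is 0.747ⁿ: 31% at n = 4, 17% at 6, 10% at 8, 0.3% at 20. The treatment coefficient could not be estimated in fewer than 0.1% of trials in any scenario.

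**The case against.** The best answer is that the article does not specify maximum likelihood. It names three covariates and SAS, which also offers penalised, exact and conditional fits. Estimator, centre coding and pooling are details that an unseen analysis plan may settle. That stands, and it is why the point is conditional. It does not dispose of it: logistic regression written without qualification in SAS ordinarily means maximum likelihood, and the covariate list and expected counts are fixed in the article itself.

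The other objections concern consequence, and they largely stand:

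- The model is supplementary. The primary result is the CMH test with a risk difference, and the article nowhere names an odds ratio as a reported quantity.
- The bias is modest against sampling error: about 0.16 on the log scale against a standard error of about 0.51, roughly a third of one standard error.
- Firth is one remedy among several. Conditional logistic regression, pooled centres and a random centre effect were not compared here.

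Four stronger readings are tempting, and the documents do not support them:

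- *The check systematically favours SFHS.* The bias is away from the null, so it enlarges whichever effect is real and vanishes when there is none. It cannot manufacture support for an ineffective product.
- *The odds ratio is overstated by about 20% as a property of the plan.* That figure depends on the estimator, on fixed centre terms and on the 88%/48% rates.
- *The model may fail.* Only coefficients of single-outcome centres diverge, and how often depends on centre sizes that the article does not give.
- *The secondary logistic models have the same problem.* Section 2.10 uses them only where adjustment is needed, and the article gives no expected day-7 relief or cure rates from which to judge sparsity.

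**Conclusion.** The concern holds in a limited, conditional form. With seven terms and about 30 expected non-relieved participants, an ordinary maximum-likelihood fit would give a treatment odds ratio about 17–25% too high at the planned rates and about 7–11% too high at 70–78% against 48%. It would give no bias under no effect. Firth's method brings the estimate close to the true value, with smaller root-mean-square error. Small centres can produce non-finite centre coefficients without losing the treatment estimate.

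Severity is low. The primary test, the risk difference and the qualitative answer of the robustness check are not threatened; only the size of a supplementary odds ratio is. The figures rest on centre entered as five fixed terms, CSS entered linearly, the article's planning rates, and assumed CSS distribution, covariate effects and centre sizes. They would be smaller if the true effect is smaller than planned.

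**What to change.** State in section 2.10, or in the analysis plan before unblinding, that the supplementary logistic model will be fitted by Firth's penalised likelihood, using the FIRTH option in SAS PROC LOGISTIC. Use a penalised profile-likelihood 95% confidence interval and report that odds ratio in place of the ordinary maximum-likelihood one. Leave the CMH test and risk difference as they are.

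The cost is one option in software already named and one sentence of text. It also gives finite estimates when a centre has only one outcome. The downside for the sponsor is a slightly less favourable odds ratio.
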